## Abstract

**Background:**

Subjective cognitive decline (SCD) is a preclinical condition associated with an increased risk of dementia and Alzheimer’s disease, with no consensus regarding effective therapeutic interventions to date. As the global burden of aging-related neurodegenerative diseases continues to rise, early intervention has become increasingly critical. Cognitive training has been proposed as a promising behavioral intervention; however, few studies have integrated multimodal assessments to elucidate its underlying neurobiological and psychological mechanisms, particularly within the educational system that shapes cognitive reserve and learning strategies across the lifespan. This pilot study aims to estimate effect sizes for future definitive trials, assess the feasibility and acceptability of the intervention and multimodal evaluations, and generate hypotheses regarding the relationship between recitation practice and clinical biomarkers.

**Methods:**

A total of 60 individuals with subjective cognitive decline will be enrolled in a randomized, assessor-blinded, controlled pilot study. Participants will be randomly assigned to either an intervention group or a non-active control group prior to baseline assessment. The intervention group will undergo a six-month structured recitation training program. Both groups will undergo short-term follow-up after the intervention, and long-term follow-up annually post-intervention. Multimodal assessments will include neuropsychological testing, functional magnetic resonance imaging (fMRI), electroencephalography (EEG), blood biomarker profiling, gut microbiota analysis, and fecal metabolomics.

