The study is designed as a randomized, assessor-blinded, controlled pilot study. A stratified block randomization sequence will be generated by an independent statistician using computer-generated random numbers, with stratification by age and sex to ensure balanced group allocation. Block sizes will be randomly varied to prevent predicting upcoming assignments. Allocation concealment will be ensured using the Sequentially Numbered, Opaque, Sealed Envelopes method; envelopes will be prepared and safeguarded by personnel not involved in recruitment, eligibility assessment, or intervention delivery. After eligibility assessment and informed consent are completed, a designated research assistant — otherwise uninvolved in outcome assessment — will open the envelope to reveal group assignment. Prior to allocation disclosure, all research personnel will remain blinded to the randomization sequence. Given that the intervention is behavioral in nature, complete blinding of participants and interventionists is not feasible. However, several measures will be implemented to minimize performance bias. Participants will be instructed not to discuss their group assignment with outcome assessors. Interventionists will have no role in outcome measurement or data analysis. Outcome assessors — including neuropsychological evaluators (psychologists) and radiologic technologists — will be formally blinded to group allocation throughout the trial and will be kept separate from the intervention team. To maintain blinding integrity, assessors will be reminded of their blinded status at each assessment visit, and any unblinding events will be documented and reported. Data analysts will similarly remain blinded to group assignment until the primary analysis is complete. The inherent risk of performance bias arising from participant awareness of group assignment will be mitigated by standardizing intervention protocols, using objective outcome measures where possible, and monitoring for differential dropout between groups.

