Following completion of the initial six-month intervention phase, participants will be given the option to voluntarily continue recitation practice. The selection of a six-month intervention period is informed by the MEMO+ (Méthode d’Entrainement pour Mémoire Optimale) protocol developed by Sylvie Belleville and colleagues (Bier et al., 2015). Later studies from the same research team have demonstrated that participants receiving structured cognitive training exhibited significant improvements in memory recall performance, with effects persisting for at least 6 months post-intervention (Belleville et al., 2018). Furthermore, long-term follow-up over 5 years revealed that individuals who had undergone cognitive training experienced a slower decline in delayed memory performance and Montreal Cognitive Assessment (MoCA) scores compared with control groups (Belleville et al., 2024). These findings underscore the sustained benefits and potential long-term impact of continuous cognitive training.

Additional support for the selected intervention duration is derived from studies examining other forms of cognitively engaging activities. For example, interventions involving structured calligraphy practice have demonstrated that extending training duration over a six-month period leads to significant alterations in functional brain connectivity (Lee et al., 2024). Specifically, increased connectivity has been observed between the medial prefrontal cortex (mPFC) and right lateral temporal cortex (LTC), mPFC and right inferior parietal lobe (IPL), left hippocampal formation (HF) and right LTC, as well as between the left HF and right IPL (Lee et al., 2024). These findings suggest that prolonged engagement (6 months) in cognitively demanding tasks may induce measurable neuro-modulatory effects at the network level.

Taken together, a 6-month intervention period represents a balanced design choice: it is sufficiently long to allow for detectable behavioral and neurobiological changes, yet not so prolonged as to compromise participant adherence. Accordingly, outcome assessments will be conducted at baseline (time of recruitment), immediately after the six-month intervention, and at one-year and two-year follow-ups, with annual assessments thereafter until participants are no longer able to complete evaluations. The study will be conducted at China Medical University Hospital, primarily within the outpatient clinics of the Departments of Neurology or Psychiatry.

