##### Statistical analysis

2.5.2.5

Statistical analyses will be conducted within the framework of the general linear model (GLM). For the primary clinical outcomes (e.g., subjective cognitive measures, neuropsychological test scores), a linear mixed-effects model will be used to handle the repeated-measures structure of the data throughout baseline, post-intervention, and follow-ups, with time, group, and group × time interaction as fixed effects, and subject as a random effect. This approach naturally accommodates missing data under the missing-at-random (MAR) assumption without requiring complete cases. The primary analysis will follow the intention-to-treat principle, including all randomized participants regardless of adherence or dropout, with missing values handled using multiple imputation based on baseline characteristics and available follow-up data. A per-protocol sensitivity analysis will also be conducted, restricted to participants who complete at least 80% of the intervention sessions. Covariates to be included in adjusted models will comprise age, sex, years of education, and baseline cognitive scores, selected *a priori* for their known associations with cognitive outcomes in SCD populations.

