Despite growing evidence for the general benefit of cognitive interventions in aging, the magnitude and consistency of effects vary substantially across trials, limiting the conclusions that can be drawn from aggregate findings. A comprehensive systematic review of interventions specifically targeting SCD found that, while cognitive training yielded a small statistically significant improvement in objective performance overall (*g* = 0.13, 95% CI 0.01 to 0.25), effect sizes became non-significant when studies used active control groups (*g* = 0.02) or reported global cognitive outcomes (*g* = 0.06), indicating that published effects may largely reflect expectancy and practice artifacts rather than genuine cognitive benefit (Roheger et al., 2021). Heterogeneity of effects is attributable to multiple sources, including variability in SCD diagnostic criteria, differences in intervention dosage and delivery format, inconsistent outcome measurement across domains, and the absence of standardized follow-up periods. In addition, the methodological quality of published cognitive intervention trials in SCD and related preclinical populations remains a significant concern. The majority of trials suffer from one or more of the following limitations: inadequate sample sizes, short intervention durations with no long-term follow-up, outcomes measured only on trained tasks rather than ecologically valid measures, high or unclear risk of bias due to lack of assessor blinding, and failure to conduct intention-to-treat analyses (Roheger et al., 2021). Beyond sample size and reporting concerns, cognitive intervention trials face several systematic biases that may inflate apparent treatment effects. The most pervasive is performance bias from expectancy effects, in which participants believe they are receiving an active intervention and therefore may perform better on outcome assessments regardless of the intervention’s true efficacy. A systematic review of computerized cognitive training trials in healthy older adults found that only 47% included an active control condition, and only 21% measured participants’ expectations — meaning that the majority of published positive findings cannot rule out expectancy as a major contributor to the observed effects (Masurovsky, 2020). To address the gap limited by short follow-up periods, inadequate control of participant expectancy effects, and a predominant reliance on behavioral outcomes without accompanying biological measures in previous studies, this pilot study will incorporate long-term annual follow-ups, administer the credibility and expectancy questionnaire to monitor and statistically adjust for expectancy at baseline and post-intervention, and employ a multimodal assessment framework integrating cognitive, neuroimaging, metabolomic, and gut microbiota measures.

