To address expectancy-related bias, the present study acknowledges that participants in the intervention group may attribute cognitive improvements to the mere receipt of a structured program rather than to its specific active components — a cognitive placebo effect that cannot be fully disentangled from true intervention effects in the absence of an active control condition. We therefore incorporate validated credibility and expectancy questionnaires administered at baseline and post-intervention to enable statistical adjustment for potential influences on outcomes. Participant expectancy will also be assessed at enrollment to characterize the degree to which anticipation of benefit may have influenced self-reported outcomes. Future definitive clinical trials should employ an active control condition that matches the intervention in time, attention, and participant engagement to better isolate the specific effects of the intervention and reduce the risk of biases.

The risk of cross-group contamination should also be acknowledged. As participants are recruited from overlapping settings — including outpatient departments and community centers — individuals assigned to the control group may become aware of the intervention content through social interaction with participants in the intervention group. This could attenuate between-group differences and lead to an underestimation of true intervention effects. To minimize this risk, participants will be reminded at enrollment and throughout the trial not to discuss study procedures with others. Future trials should consider cluster randomization or geographically separated recruitment sites to further reduce the risk of contamination.

The cultural and linguistic specificity of the intervention represents an additional limitation. The cognitive training program incorporates Traditional Chinese poetry recitation, a practice deeply embedded in Taiwanese cultural and educational traditions. The cognitive demands, memorability, and emotional engagement associated with this material may not translate equivalently to populations with different linguistic backgrounds or cultural relationships to classical literary forms. Accordingly, the generalizability of findings to non-Chinese-speaking populations may be limited. Adaptation and revalidation of the intervention content are required before international replication.

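### Allocation may be known before baseline is measured, and adjusting for post-intervention expectancy would not give the total randomised effect

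*Protocol article*

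**What the plan says.** On timing, the Abstract (Methods) reads: "Participants will be randomly assigned to either an intervention group or a non-active control group prior to baseline assessment". Section 2.1 gives the trigger for disclosure: "After eligibility assessment and informed consent are completed, a designated research assistant", otherwise uninvolved in outcome assessment, "will open the envelope to reveal group assignment". A completed baseline is not a condition. The same section concedes that "complete blinding of participants and interventionists is not feasible". Near its end, section 2.1 also says that "outcome assessments will be conducted at baseline (time of recruitment), immediately after the six-month intervention", without saying whether recruitment comes before or after the envelope is opened.

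On adjustment, section 2.5.2.5 fixes the list: "Covariates to be included in adjusted models will comprise age, sex, years of education, and baseline cognitive scores". Expectancy is not on it. Section 3.1, however, says that the study will "administer the credibility and expectancy questionnaire to monitor and statistically adjust for expectancy at baseline and post-intervention", and section 3.2 describes "validated credibility and expectancy questionnaires administered at baseline and post-intervention to enable statistical adjustment for potential influences on outcomes". Section 3.2 adds that expectancy will be assessed at enrolment, again without placing this relative to disclosure.

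**The concern.** Two separate matters are involved.

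The first is timing. If a participant knows the arm when T0 is measured, T0 is no longer a pre-allocation measurement. Effort on cognitive tests and stated expectancy can respond to that knowledge, and blinding the assessor does not prevent it. T0 is the first time point of the mixed model in 2.5.2.5, supplies the baseline cognitive covariate, and is the reference for the T0-to-T1 changes in 3.3. A difference between arms that disclosure creates at T0 would enter all of these.

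The second is the covariate. Expectancy after six months comes after treatment and can be changed by the training itself or by perceived improvement. Conditioning on it can remove part of the effect, or introduce bias if expectancy and outcome share an unmeasured cause.

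The trial exists partly to supply effect sizes for later definitive trials (Abstract; 2.1). A distorted contrast would carry forward into their sample sizes.

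**Working it through.** **Order of events, as documented**

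- Before disclosure: objective cognitive testing for eligibility, including the MoCA and an exclusion based on any cognitive domain (2.2); EEG and structural MRI, which 2.5.2 places before enrolment.
- Disclosure: after eligibility and consent (2.1).
- After disclosure, if the Abstract is followed: whatever part of the baseline assessment was not done at screening. That may include the expectancy questionnaire, neuropsychological tests not needed for eligibility, fMRI, blood and stool.
- Unresolved: baseline at recruitment (2.1) and expectancy at enrolment (3.2). Either could fall on either side of disclosure.

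**The plan's own figure**

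Section 2.3 uses d = 0.18, one-sided alpha 0.05 and power 0.80, and reports 383 per group with power 0.8006. The exact noncentral t calculation returns 383 and 0.8006. The figure is not in dispute. Only 0.18 is taken from it, as a yardstick; it belongs to a neuropsychological scenario that 2.3 sets aside as infeasible.

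**Effect of a T0 shift**

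Assumptions, none from the documents: disclosure shifts T0 by b SD (intervention minus control), the six-month effect stays at 0.18 SD, and baseline and follow-up correlate at r = 0.7.

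- Change contrast (also the group × time contrast with T0 as a response): 0.18 − b.
- Baseline as covariate: 0.18 − r × b.

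| b | Change contrast | Baseline-adjusted |
|---|---|---|
| −0.10 | 0.18 + 0.10 = 0.28 | 0.18 + 0.07 = 0.25 |
| 0 | 0.18 | 0.18 |
| 0.05 | 0.13 | 0.18 − 0.035 = 0.145 |
| 0.10 | 0.08 | 0.18 − 0.07 = 0.11 |
| 0.20 | −0.02 | 0.18 − 0.14 = 0.04 |

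The full shift applies only to the change contrast. The sign of the bias follows the sign of b, and with b = 0 there is none.

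**Effect of adjusting for post-intervention expectancy**

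Assumptions, again not from the documents: training raises expectancy by e SD, and expectancy has slope s on the outcome. The total effect is 0.18; the adjusted estimate is 0.18 − s × e.

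- e = 0.3, s = 0.1: 0.18 − 0.03 = 0.15.
- e = 0.5, s = 0.2: 0.18 − 0.10 = 0.08.
- e = 0.8, s = 0.3: 0.18 − 0.24 = −0.06.

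Now let s = 0, with an unmeasured cause loading 0.3 on both expectancy and outcome. The adjusted estimate becomes 0.18 − 0.3 × 0.3 × e, which is 0.153 at e = 0.3 and 0.108 at e = 0.8. So bias can arise even when expectancy has no effect on the outcome. With s = 0 and no shared cause, there is none.

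A simulation of one million participants agreed with these formulas to within 0.003.

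**The case against.** A reader might infer that every baseline measure is taken with the arm known. The documents do not support that. Eligibility testing and the EEG precede disclosure, and 2.5.2.5 does not say that its baseline cognitive scores are post-disclosure ones. Section 2.1 can also be read as placing baseline at recruitment, before the envelope. This narrows the point to measures not taken at screening, but it does not remove it: the Abstract states the opposite order, and no section makes T0 a condition for disclosure.

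A reader might also infer that the specified primary model includes post-intervention expectancy. It does not. Expectancy is missing from the covariate list in 2.5.2.5, the group-level imaging comparisons in 2.5.2.5 are two-sample tests with no expectancy term, and the adjustment wording appears only in the Discussion. In 3.1 the timing phrase could describe when the questionnaire is given, and 3.2 speaks only of enabling adjustment. What stands is that both sections attach adjustment to a questionnaire given at both times and do not label it as a sensitivity or mediation analysis.

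Nor is bias at T0 established. It needs knowledge of the arm to alter the measurement, and the documents give no reason why resting-state fMRI, blood or stool would respond. Loss of disappointed controls before T0 is possible but speculative: 2.1 monitors differential dropout, and 3.2 enrols only people willing to complete the assessments.

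Finally, this is a pilot with feasibility as its main aim. With 30 per arm, the standard error of an unadjusted standardised difference is √(1/30 + 1/30) = 0.26 SD, larger than any bias assumed above. That limits what the pilot estimate can show, but it is no reason to keep a source of bias that reordering the steps would remove.

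**Conclusion.** The concern holds in limited form. Followed as written, the Abstract and 2.1 allow some T0 measures to be collected from participants who know their arm, and the timing statements are not reconciled. This is an avoidable risk of bias, of unknown direction and size, in T0-to-T1 contrasts and baseline-adjusted models. It is most plausible for expectancy and effort-dependent cognitive scores, and least plausible for resting-state fMRI, blood and stool.

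The firmer fault is the planned adjustment for post-intervention expectancy. Whatever the timing of baseline, an estimate adjusted for it is not the total randomised effect, although the document does not fix which model would use it.

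The sizes are illustrations on assumed inputs. T0 shifts of 0.05 to 0.20 SD move a baseline-adjusted estimate by 0.035 to 0.14 SD and a change contrast by the full shift. Expectancy adjustment takes 0.18 to between 0.15 and −0.06 over the assumed range without a shared cause. No figure in the protocol is numerically wrong because of this point.

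**What to change.** 1. State in the Abstract and section 2.1 that the envelope is opened only after all T0 assessments are complete (neuropsychology, expectancy, fMRI, EEG, blood, stool). Reconcile this with the statement in 2.1 that baseline falls at recruitment, and place the enrolment expectancy measure in 3.2 before disclosure.
2. In 2.5.2.5, specify that baseline covariates are pre-allocation cognitive scores. If expectancy is adjusted for, use only the pre-allocation measure.
3. Remove post-intervention expectancy from the adjustment statements in 3.1 and 3.2. Report it by arm descriptively, or use it only in a labelled exploratory mediation or sensitivity analysis.

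Cost: training starts slightly later, and a few people will complete T0 without being randomised. No new procedure is needed. Stratification uses only age and sex, both known at screening, so it does not stand in the way. The third change is to wording only.

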**Discussion:**

This study protocol outlines a randomized, assessor-blinded, controlled pilot study designed to advance understanding of the feasibility of Chinese Classics recitation training on both physiological and psychological outcomes in individuals with subjective cognitive decline. The findings are expected to provide mechanistic insights into non-pharmacological interventions and to address the current underrepresentation of Asian populations in neuroscience research.

**Clinical trial registration:**

We registered this randomized controlled trial on ClinicalTrials.gov on March 11, 2026, under the identifier NCT07463391.

## Introduction

1

Dementia, a progressive neurodegenerative condition strongly associated with aging, imposes substantial social, economic, and familial burdens worldwide. Its prevalence is projected to continue rising, posing significant challenges to global public health systems (Liu et al., 2025). In Asia, the increase has been particularly pronounced: from 1990 to 2021, the incidence, prevalence, and mortality of Alzheimer’s disease (AD) and related dementias increased by 244.73, 250.44, and 297.34%, respectively (Guo et al., 2025). These alarming trends underscore the urgent need for early identification and intervention strategies targeting preclinical stages of cognitive decline.

Subjective cognitive decline (SCD) was formally conceptualized in 2014 to describe a self-reported experience of cognitive deterioration in individuals who perform normally in objective and standardized neuropsychological tests (Jessen et al., 2020). The trajectories of SCD are heterogeneous, ranging from reversible or stable forms to progressive phenotypes that evolve into mild cognitive impairment (MCI) and eventually dementia (Jessen et al., 2020). A meta-analysis reported that approximately 14% of individuals with SCD developed dementia over a four-year follow-up period (Mitchell et al., 2014). Despite its clinical significance as a potential preclinical stage of neurodegeneration, no pharmacological treatments are currently approved specifically for SCD (Smid et al., 2022).

For patients with established dementia, current treatment approaches broadly fall into biological and behavioral domains. Pharmacological management commonly includes cholinesterase inhibitors, such as rivastigmine, and N-methyl-D-aspartate receptor antagonists, such as memantine (Byeon et al., 2025). In 2021, the U. S. Food and Drug Administration approved aducanumab (Aduhelm), an amyloid-targeting monoclonal antibody, marking a milestone in disease-modifying therapeutic development for Alzheimer’s disease. Subsequently, lecanemab demonstrated greater clinical efficacy in reducing cognitive decline and cerebral amyloid burden compared to placebo (van Dyck et al., 2023). However, treatment with amyloid-targeting antibodies has been associated with amyloid-related imaging abnormalities, including cerebral edema and microhemorrhage, particularly among individuals who are apolipoprotein E ε4 homozygotes (van Dyck et al., 2023). These safety concerns highlight the continued importance of developing non-pharmacological interventions with favorable risk–benefit profiles, especially for individuals at earlier stages such as SCD.

Cognitive training represents one of the most extensively studied behavioral interventions for SCD. A meta-analysis of 16 randomized controlled trials reported that cognitive training interventions were associated with improvements in individuals with SCD, with no significant statistical heterogeneity detected across studies (Bhome et al., 2018). Notably, statistically significant improvements were primarily observed when interventions were compared with non-active control groups that lacked structured cognitive stimulation (Bhome et al., 2018). This finding suggests that external cognitive engagement may be a critical factor in driving measurable benefits. Despite accumulating evidence supporting non-pharmacological approaches, research tailored to Asian populations remains limited. Among the trials included in the aforementioned meta-analysis, only one study specifically focused on individuals whose primary language was Chinese (Tsai et al., 2008). This disparity highlights a shortage of culturally and linguistically adapted cognitive intervention research for Chinese-speaking populations. In contrast to other neurological assessments, such as muscle strength evaluation, the assessment of higher cortical functions is inherently culture-dependent (Rosselli et al., 2022). For example, in the Boston Naming Test, items such as igloo and harp may be relatively unfamiliar to Chinese participants, whereas the abacus—often considered one of the more challenging items for American participants—is widely recognized among many Chinese individuals (Li et al., 2022).

More recent investigations have further demonstrated that non-pharmacological interventions, including cognitive training, transcranial direct current stimulation, balance exercises, music therapy, and mindfulness-based therapies, are associated with overall positive effects in individuals with SCD (Yu X.-H et al., 2024). However, few studies have incorporated multimodal biological assessments to elucidate the mechanistic pathways underlying observed behavioral improvements.

Classical recitation constitutes a multimodal cognitive activity that concurrently engages phonological, articulatory, semantic, and auditory self-monitoring circuits. Evidence from functional MRI confirms that recitation activates the primary motor cortex, supplementary motor areas, Broca’s area, Wernicke’s area, and the superior temporal gyrus — regions critically susceptible to age-related decline in SCD (Ranjan and Singh, 2025). Sustained verbal training in older adults has been demonstrated to enhance frontotemporal and hippocampal functional connectivity, with articulatory exercises specifically reinforcing the phonological retrieval networks most affected by aging (Yang et al., 2022). At the network level, structured verbal-attentional practice fortifies intrinsic connectivity within the default mode network — particularly between the hippocampus and posteromedial cortex — which is the network most selectively disrupted in preclinical Alzheimer’s disease (Sevinc et al., 2021).

The proposed pathway from recitation to gut microbiota modulation is mediated through autonomic nervous system regulation. Focused, rhythmic vocalization reduces hypothalamic–pituitary–adrenal (HPA) axis reactivity and enhances vagal tone, thereby attenuating stress-driven gut dysbiosis (Jabbari Shiadeh et al., 2025). Sustained psychological stress has been shown to alter neurotransmitter release and disrupt intestinal epithelial homeostasis by blocking protective vagal nerve barrier effects, shifting microbial composition toward pro-inflammatory profiles (Ningthoujam et al., 2021). Conversely, mind–body practices that enhance vagal tone are associated with healthier gut microbiota diversity and reduced pro-inflammatory bacteria. The mechanistic link between gut microbiota and brain plasticity operates primarily through microbial metabolites, as emerging evidence highlights the critical role of the gut-brain axis, a complex bidirectional network involving neural, endocrine, immune, and metabolic pathways (Tsai et al., 2025). Within this framework, gut microbiota has been shown to influence blood–brain barrier integrity, neuroplasticity, and cognitive function through the production of short-chain fatty acids, modulation of neurotransmitter precursors, and regulation of systemic inflammation (Agirman and Hsiao, 2021; Zhang et al., 2023). For instance, gut bacteria produce butyrate, acetate, and propionate, which cross the blood–brain barrier and upregulate the CREB/BDNF signaling pathway, promoting neuronal repair, memory consolidation, and synaptic plasticity, while suppressing neuroinflammation via inhibition of MAPK and NF-κB (Qian et al., 2022). In parallel, microbial tryptophan metabolism yields indole derivatives and kynurenine pathway intermediates that modulate serotonin synthesis and glutamatergic signaling — both critical for hippocampal neuroplasticity (Connell et al., 2022). Recent advances in whole-blood metabolomics have further identified disease-associated metabolic signatures in individuals with dementia (Teruya et al., 2021), underscoring the potential of metabolic profiling as a tool for early detection. These findings collectively suggest that alterations in the gut-brain axis may occur in the preclinical stages of cognitive decline. However, a direct causal link between classical recitation and modulation of the gut microbiome has not yet been established in any interventional trial, and whether cognitive training prevents or delays cognitive decline by protecting gut microbiota composition and metabolic profiles, particularly in individuals with SCD, has not been systematically investigated. Therefore, decoding how cognitive interventions modulate the degenerative interactions of gut-brain axis will generate significant impacts on preventive medicine.

Cognitive training programs often incorporate culturally tailored elements to enhance acceptability and engagement among participants. In practice, training materials delivered in English may be ineffective for individuals who do not understand the language. However, culturally matched cognitive training programs remain scarce in Chinese-speaking societies despite rapid demographic aging and the growing burden of dementia. Therefore, this study with Chinese cognitive training materials investigates whether this culture-match, structured cognitive training is related to outcomes in individuals with SCD and examines potential neurobiological and systemic correlates of any observed effects, such as blood inflammation marker (cortisol). Specifically, we propose to evaluate the impact of Chinese Classics recitation training through comprehensive multimodal assessments, including neuropsychological testing, functional magnetic resonance imaging (fMRI) (Rajah and D'Esposito, 2005; Anthony and Lin, 2018), electroencephalography (EEG) (Yu W. Y. et al., 2024), blood biomarker profiling (Teruya et al., 2021), and gut microbiota (Kuijer and Steenbergen, 2023) and fecal metabolomic analyses (Zhao et al., 2025). By integrating behavioral intervention with advanced neuroimaging and biomarker methodologies within a culturally grounded educational framework, this study seeks to address current gaps in the literature and provide population-specific evidence relevant to Chinese-speaking communities. Such an approach may contribute to the development of precision-oriented, low-risk intervention strategies for early cognitive decline in aging populations. We will primarily aim to evaluate the feasibility and acceptability of classical recitation training in older adults with subjective cognitive decline. As a secondary objective, we will investigate whether recitation training correlates with changes in neuroimaging markers associated with brain plasticity. Additionally, exploratory objectives include characterizing metabolomic and gut microbiota profiles and examining their potential associations with cognitive and neuroimaging outcomes. These exploratory analyses are designed to generate preliminary data and inform future hypothesis-driven research exploring potential pathways linking recitation training, gut-brain interactions, and neuroplasticity, representing a novel mechanistic framework.

